# Enhanced versus standard blood pressure lowering on intracranial aneurysm rupture or growth (ChATIA-1 trial): protocol for a multi-centered, prospective, open-label randomized controlled trial

**DOI:** 10.3389/fneur.2025.1627936

**Published:** 2026-01-07

**Keywords:** unruptured intracranial aneurysm, blood pressure, aneurysm instability, rupture, growth

## Abstract

**Background:**

Hypertension is a common comorbidity in patients with unruptured intracranial aneurysms, which is closely related to the instability of aneurysms. Though anti-hypertension therapy has been recommended by several guidelines, the optimal blood pressure range remains unknown. This trial aims to determine the optimal range of blood pressure by comparing standard blood pressure reduction and intensive blood pressure reduction to reduce the instability of unruptured intracranial aneurysms.

**Methods/design:**

This trial is a multicenter, prospective, open-label, randomized controlled trial with minimization to ensure allocation concealment. Five hundred seventy patients with unruptured intracranial aneurysms and hypertension will be recruited by nine centers in China. Patients will be allocated to the standard blood pressure lowering (SBPL) group (systolic blood pressure at 120–140 mmHg) or the enhanced blood pressure lowering (EBPL) group (systolic blood pressure at <120 mmHg). The primary outcome is aneurysm instability within 24 months after appropriate blood pressure lowering therapy, including aneurysm growth and aneurysm rupture. During follow-up, Blood pressure data will be collected monthly, while radiological examination for aneurysms will be performed at 6 ± 1 months, 12 ± 1 months and 24 ± 1 months. The trial has 85% power to reduce 60% of aneurysm instability.

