### Statistical analysis

#### Sample size

The sample size is estimated using the PASS 15 (PASS Corporation, United States). In our preliminary studies, the 2-year instability events risk was approximately 20.7% in UIA patients with hypertension and 11.5% in UIA patients with controlled hypertension (17). In this study, we assume that EBPL could decrease the risk of aneurysm rupture and growth by 50%. At *α* = 0.05, *β* = 0.90, we need to enroll 506 patients (253patients in the SBPL group and 253 patients in EBPL group). By estimating the clinical dropout rate at 10%, the required sample size was calculated to be 282 patients in each group. This study prepared to include 570 patients in both groups (285 in each group), which could meet the statistical requirements.

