#### Endpoint and outcome evaluation

Before locking the database for analysis, we intend to test its plausibility and effectiveness. We will exclude the cases that could influence the accuracy of the conclusion. Patients who do not meet the requirement of quality control may be further excluded based on the consensus of the investigators’ discussion.

Categorical variables are presented as numbers (no.) and percentages (%). Continuous variables with normal distribution are expressed as means and standard deviation, and medians and inter-quartile range (IQR) if otherwise. The differences between groups in continuous variables are compared by performing the student’s t-tests or Wilcoxon rank sum tests, and the differences in categorical variables are compared using the chi-square tests or Fisher’s exact tests. The incident rate (IR) of PR and its 95% confidence interval (CI) are calculated. The univariate and multivariate Cox regression analyses are performed in PR-related analysis. The result of Cox regression analysis is presented as hazard ratio (HR) and 95% CI. SPSS 24.0 (SPSS, Chicago, IL) is used for statistical analysis, and bilateral *p* < 0.05 is considered statistically significant.

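### The abstract (85% power, 60% reduction) and the sample-size section (50% reduction, β written as 0.90) state different designs for the same 570 patients, and neither names the control risk

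*Protocol article*

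**What the plan says.** The Methods/design paragraph of the abstract gives 570 patients and then: "The trial has 85% power to reduce 60% of aneurysm instability". It states no control risk.

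The Sample size section quotes two preliminary figures: "the 2-year instability events risk was approximately 20.7% in UIA patients with hypertension" and "11.5% in UIA patients with controlled hypertension". It continues "we assume that EBPL could decrease the risk of aneurysm rupture and growth by 50" per cent, and sets β to "0.90, we need to enroll 506 patients", that is "253patients in the SBPL group and 253 patients in EBPL group". With 10% dropout this becomes 282 per arm, and 285 per arm (570 in total) are planned. The section does not say which of the two preliminary risks is the assumed risk in the standard (SBPL) arm.

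The test is two-sided according to Endpoint and outcome evaluation: "bilateral *p* < 0.05 is considered statistically significant". Allocation is 1:1 (Step 2: Randomization and intervention).

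**The concern.** Both statements are current text about one trial, one sample size and one 24-month instability endpoint, yet they give different power (85% against 90%) and different effects (60% against 50%). Condensation into an article does not explain this, because both sets of figures are printed.

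The symbol is also wrong. β is the type II error rate, so 0.90 belongs to power.

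What is at stake is the reading of a neutral result. A trial with 90% power for a 50% reduction excludes more than one with 85% power for a 60% reduction. The mismatch also draws attention to an unnamed input, the control risk, on which every power figure depends.

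**Working it through.** **Inputs.** Candidate control risks 20.7% and 11.5%; relative reductions 50% (Sample size) and 60% (abstract); 253, 282 and 285 per arm; dropout 10% (all from Sample size unless noted); two-sided α = 0.05, so z = 1.960; 1:1 allocation. Power 0.90 gives z = 1.282.

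**Step 1: reproduce the plan's own number.** Take 20.7% and halve it: p1 = 0.207, p2 = 0.1035.

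Unpooled formula: n = (1.960 + 1.282)² × [p1(1 − p1) + p2(1 − p2)] / (p1 − p2)²

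= 10.507 × (0.16415 + 0.09279) / 0.010712 = 252.03, rounded up to **253 per arm**, as stated.

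The pooled-variance version gives 255.2, so 256. Dropout: 253 / 0.90 = 281.1, so **282**, as stated. The section is therefore internally sound once β = 0.90 is read as power = 0.90. Read literally (power 0.10), the same formulas would need only about 12 per arm.

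**Step 2: analysed number.** 285 × 0.90 = 256.5, about 257 per arm.

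**Step 3: power.** Pooled formula, with p̄ the mean of p1 and p2:

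power = Φ{ [(p1 − p2)√n − 1.960 √(2p̄(1 − p̄))] / √(p1(1 − p1) + p2(1 − p2)) }

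Example, 20.7% versus 8.28% (60% reduction) at n = 257: (1.9911 − 0.9757) / 0.4900 = 2.072, so power is 98.1%.

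Example, 11.5% versus 4.6% (60% reduction) at n = 285: (1.1649 − 0.7541) / 0.3817 = 1.076, so power is 85.9%.

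| Control risk | Reduction | 253 per arm | 257 per arm | 285 per arm |
|---|---|---|---|---|
| 20.7% | 50% | 89.8% | 90.2% | 92.9% |
| 20.7% | 60% | 97.9% | 98.1% | 98.9% |
| 11.5% | 50% | 63.5% | 64.2% | 68.7% |
| 11.5% | 60% | 81.6% | 82.2% | 85.9% |

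The unpooled formula moves these by less than half a percentage point (for instance 90.1% in place of 89.8% in the first cell).

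**Step 4: where could the abstract's figure come from?** At 20.7%, 85% power for a 60% reduction needs only 143 per arm (pooled), so the planned numbers do not fit. At 11.5% it needs 278 per arm, which 285 meets only if almost nobody is lost. Solving for the control risk that gives exactly 85% power at a 60% reduction returns about 11.2% with 285 per arm and about 12.5% with 253 per arm. Separately, 20.7% versus 11.5% at 285 per arm gives 85.0% power, but that is a reduction of 1 − 11.5/20.7 = 44%, not 60%.

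**The case against.** The strongest reply is that this is a reporting slip. The total of 570 is the same in both places, the Sample size section is the operative calculation and it reproduces, and no reader would take β = 0.90 to mean a trial planned at 10% power. Correcting the mismatch alone changes no enrolment, endpoint or test. All of that stands, and it is why the repair is cheap. It does not make the abstract's sentence consistent with the calculation.

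Three stronger readings are tempting, and the documents do not support them.

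- **That the two statements demonstrably rest on different control risks.** The abstract names none, and the Sample size section does not label the one it used. The arithmetic makes this likely, but the 44% scenario also yields 85%, so the origin of that figure is unknown.
- **That neither statement describes the trial after dropout.** At 20.7% the Sample size design does: 90.2% at 257 per arm.
- **That the SBPL arm's risk is 11.5%.** The article does not define controlled hypertension in the preliminary data or equate it with the SBPL target of 120–140 mmHg. The 11.5% figure is a reasonable sensitivity value because SBPL patients are treated, but it is not an established planning value.

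**Conclusion.** The concern holds as an inconsistency in stated power and effect, together with a mislabelled β. On the design that reproduces (20.7% versus 10.35%, two-sided 0.05), power is 90% for a 50% reduction with about 257 analysed per arm, and a 60% reduction would have about 98%. The abstract's 85% is therefore about 13 points below what that calculation gives for the effect it names. If its basis was 11.5%, it is about 3 points too high after the plan's own 10% dropout.

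These figures rest on a two-proportion normal approximation, on 20.7% being the planned control risk (inferred from the exact match to 253), and on 10% loss in each arm. Which control risk the sponsor intended remains open. It matters: for the 50% reduction, power at 257 per arm is about 90% at 20.7% and about 64% at 11.5%.

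**What to change.** Use one statement in the abstract and in Sample size that names the assumed SBPL risk, the relative reduction, two-sided α = 0.05, the power and the number analysed after dropout. Write power = 0.90 (β = 0.10).

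If the Sample size design is kept, the abstract should say: 570 randomised, about 257 per arm analysed after 10% dropout, 90% power for a 50% relative reduction from an SBPL risk of 20.7%, two-sided α = 0.05. If another control risk was intended, the sponsor should state it and redo the calculation.

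Because SBPL patients are treated, also report power at the other quoted risk, 11.5%, as a sensitivity figure: about 64% for a 50% and 82% for a 60% reduction at 257 per arm.

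The cost is wording in two places. The added figure is clearly less favourable than the stated 90%: for scale, 90% power for a 50% reduction from 11.5% would need 496 (unpooled) to 499 (pooled) analysed per arm. Reporting it does not commit the sponsor to that size, but it shows how far the claim depends on the control risk.

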**Discussion:**

The China Antihypertensive Trial for Intracranial Aneurysm (ChATIA) trial is a randomized trial about blood pressure lowering therapy for UIA patients. In this study, a new strategy and evidence will be provided for blood pressure management in the future.

**Clinical trial registration:**

http://www.clinicaltrials.gov, identifier NCT05941377.

## Introduction

Unruptured intracranial aneurysms (UIAs) are pathological dilatations of cerebral arteries that develop under the combined effects of hemodynamic stress and progressive vascular wall degeneration (1, 2). A comprehensive systematic review and meta-analysis encompassing 68 studies from 21 countries (83 cohorts, 94,912 individuals) estimated the global prevalence of UIAs in adults around 50 years of age to be approximately 3.2% (3). In China, a cross-sectional study of 4,813 Shanghai residents aged 35–75 years reported a higher prevalence of 7.0%, peaking in individuals aged 55–64 years (4). Given the catastrophic consequences of aneurysmal rupture and the procedural risks associated with prophylactic surgical or endovascular repair, optimizing medical management to prevent aneurysm growth or rupture has emerged as a critical unmet clinical need (1, 5).

Hypertension is the most prevalent comorbidity in this population (1, 6). Its influence on aneurysm instability—manifested as aneurysm growth or rupture—is profound (7). Hypertension is a well-established, independent risk factor for rupture, primarily through its augmentation of hemodynamic stress on the fragile, degenerative aneurysmal wall. This excessive pressure accelerates mural fatigue, promotes inflammatory remodeling, and ultimately compromises wall integrity (8). Consequently, hypertension is incorporated into validated rupture risk models such as the PHASES score, and its presence markedly increases rupture probability, even in small aneurysms (≤7 mm) (9). Given the central role of hypertension, strict blood pressure control constitutes a cornerstone of conservative UIA management (10, 11).

In the broader cardiovascular literature, randomized controlled trials have demonstrated the benefits of intensive blood pressure reduction. The SPRINT trial showed that targeting a systolic BP < 120 mmHg significantly decreased major cardiovascular events (12). Similarly, the STEP trial (target 110–130 mmHg) reduced major cardiovascular events, including stroke, while the BPROAD trial found that intensive BP lowering reduced such events in patients with diabetes (13, 14).

However, definitive randomized evidence specific to UIA patients remains lacking. The safety and efficacy of intensive blood pressure targets for preventing aneurysm growth or rupture have not been rigorously tested, leaving the optimal management threshold unresolved.

To address this gap, we initiated the China Antihypertensive Trial for Intracranial Aneurysm (ChATIA)—a randomized controlled study designed to evaluate the benefits and safety of enhanced blood pressure reduction in patients with unruptured intracranial aneurysms. This trial aims to establish evidence-based guidelines for blood pressure management tailored to the unique pathophysiological context of UIAs.

## Methods/design

### Study design

The ChATIA trial is a multicenter, prospective, open-label, randomized controlled trial with a minimization system to allocate patients with UIAs into the SBPL group and EBPL group at a ratio of 1:1. The primary efficacy endpoint is UIA instability, and the safety endpoint is the incident of ischemic cerebral or cardiac events. This randomized controlled trial (RCT) will follow the Consolidated Standards of Reporting Trials (CONSORT) guidelines (15).

### Patient selection

The inclusive/exclusive criteria are listed as follows:

#### Inclusion criteria

Age 18–75.Chinese ethnicity.Unruptured saccular intracranial aneurysm (UIA) identified by computational tomography angiography, magnetic resonance angiography or digital subtraction angiography.Maximal size of UIA at largest dimension < 7 mmThe morphology of UIA is regular (no bleb(s) or secondary aneurysm(s) protruding from the UIA fundus or bi−/multi-lobular UIA fundus)UIA receiving conservative treatmentHistory of primary hypertension (as diagnosed per standard of care)Systolic blood pressure (SBP) on 2 consecutive visits:SBP: 130–180 mmHg on 0 or 1 antihypertensive medication.SBP: 130–170 mmHg on up to 2 antihypertensive medications.SBP: 130–160 mmHg on up to 3 antihypertensive medications.SBP: 130–150 mmHg on up to 4 antihypertensive medicationsGood medication adherence (Morisky Medication Adherence Scale ≥6)Obtain informed consent from patient or legal representative.

##### Exclusion criteria

Patients with neurological symptom related to UIA, such as sentinel headache, oculomotor paralysis and so on.Patients with additional active intracranial disease including vasculopathy, arteriovenous malformation/fistula, cancer, traumatic brain injury etc.Patients with fusiform, dissecting, blister, traumatic, mycotic/bacterial, myxomatous, and tumor-associated UIAs are excluded.Patients with history of polycystic kidney disease, rheumatic disease or autoimmune disease.Patients with family history of intracranial aneurysm (defined when two direct relatives of patients within three generations have intracranial aneurysms or aneurysmal subarachnoid hemorrhage).Patients with known secondary cause of hypertension.Patients with myocardial infarction, ischemic stroke, symptomatic heart failure during the past 3 months.Patients with a medical condition likely to limit survival to less than 2 years.Patients during pregnancy and perinatal period.Any concurrent serious illness that would interfere with the outcome assessments including hepatic, renal, gastroenterological, respiratory, cardiovascular, endocrinologic, immunologic, and hematologic disease.Inability or unwillingness of patient or legal representative to give written informed consent.Participation in a concurrent interventional medical investigation or clinical trial.

UIA patients who meet the inclusion criteria but do not meet the exclusion criteria will be considered in subsequent randomization.

### Outcomes and relative definitions

The primary efficacy outcome is UIA instability, including aneurysm growth, rupture or aneurysm-related symptoms during 24-month follow-up. The definitions of UIA instability are listed as follows:

Aneurysm growth is defined as one or more of the following: (1) growth of more than 1 mm in at least one direction, (2) growth of more than 0.5 mm in at least two directions, (3) growth of more than 20% of baseline aneurysm size in any direction, or (4) new appearance of irregularity on the UIA.Aneurysm rupture is diagnosed when patients have the symptoms of non-traumatic subarachnoid hemorrhage (e.g., severe headache and sudden coma) attributable to the target UIA, imaging evidence of hemorrhage on CT or MRI, and/or bloody cerebrospinal fluid from lumbar puncture.Occurrence of aneurysm-related symptoms is diagnosed as sentinel headache (a sudden and severe headache attributable to the UIA within 2 weeks of onset, and without prior history of significant headache within the previous 5 years), oculomotor nerve palsy (a sudden headache with one or several symptoms of pupillary light reflex disappearing, ptosis, or extraocular myoparalysis, ipsilateral to a UIA in the vicinity of the affected oculomotor nerve and without systemic cause such as diabetes), other cranial neuropathy (such as visual field defect secondary to UIA compression of the optic apparatus without alternative cause), or seizure related to UIA inflammation (defined as EEG or clinically determined seizure activity generated from inflammatory changes in the brain parenchyma surrounding the UIA on imaging, and without prior history of seizure or other cause of seizure).

Two investigators who are unaware of the patient’s information assess the occurrence of UIA instability and ischemic brain or cardiac events at 6 months (± 1 month), 12 (± 1 month) months, and 24 (± 1 month) months through monthly follow-up and imaging examinations of UIA.

The primary safety outcome is any ischemic cerebral or cardiac events during 24-month follow-up. This includes one or more of the following: new or more frequent transient ischemic attacks, new clinical or radiological ischemic stroke, angina, new myocardial infarction, or reperfusion therapy for myocardial infarction. Ischemic brain or cardiac events are defined as follows:

TIA is defined as a transient episode (duration of symptoms < 24 h) of neurological dysfunctions caused by focal brain, spinal cord, or retinal ischemia without showing acute infarction on non-contrasted CT (NCCT).Ischemic stroke is a persistent episode of neurological dysfunctions caused by focal brain, spinal cord, or retinal ischemia, which shows acute hypodense infarction area on NCCT images and T2-weighted MRI.Angina is defined as a transient chest pain or pressure (duration of symptoms < 30 min) caused by insufficient blood flow to the myocardium without significant ST/T changes in ECG and rise of cardiac biomarkers.Myocardial infarction is defined as myocardial necrosis in clinical settings consistent with myocardial ischemia. These conditions can be satisfied by a rise of cardiac biomarkers [preferably cardiac troponin (cTn)] plus at least one of the following: (1) symptoms of cardiovascular ischemia; (2) ECG changes indicative of new ischemia (significant ST/T changes or left bundle branch block); (3) development of pathologic Q waves; (4) imaging evidence of new loss of myocardium or new regional wall motion abnormalities; (5) angiography or autopsy evidence of intracoronary thrombus.

Secondary outcomes are: 1. UIA rupture events during 24-month follow-up; 2. UIA growth events during 24-month follow-up; 3. Change in average Wall Enhancement Index (WEI) at baseline and 24th month. WEI is defined as follows:

Two investigators (with work experience of >10 years, who are blind to the clinical and morphological information) measure the WEI value independently using Vessel-MASS software (Leiden University Medical Center). Three slices with significant enhancement observed by post-contrast VW-MRI at baseline and 24 months will be selected. After tracing the lumen and outer boundaries of the aneurysm wall, the contours of the inner lumen and outer wall of aneurysms will be automatically segmented using the software. If the tracking is not satisfactory, the investigators will manually adjust the contour of the inner cavity and the outer wall. Subsequently, the mean signal intensity (SI) will be calculated automatically using the software. The average and maximum value of the mean SI of the corresponding three slices will be used for further analyses.

$$\mathrm{WEI}=\frac{\frac{\mathrm{SI}\_\mathrm{Wal}l_{\text{postcontrast}}}{\mathrm{SI}\_\text{White matte}r_{\text{postcontrast}}}-\frac{\mathrm{SI}\_\mathrm{Wal}l_{\text{precontrast}}}{\mathrm{SI}\_\text{White matte}r_{\text{precontrast}}}}{\frac{\mathrm{SI}\_\mathrm{Wal}l_{\text{precontrast}}}{\mathrm{SI}\_\text{White matte}r_{\text{precontrast}}}}$$

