### Quality control of the research

To avoid bias and ensure patients’ medical adherence, we follow the standards in the subsequent text:

Self-monitoring of blood pressure: According to the recommendation of China’s guideline for hypertension (2018) (16), we will use the home blood pressure monitoring method to monitor patients’ blood pressure monthly. All patients will receive training for blood pressure measurements from professional cardiologists at enrollment and every 3 months. We will evaluate pre-enrollment medication adherence and include only patients with good adherence. We will require all patients to measure the blood pressure of the left brachial artery twice at least 1 min apart in the morning before breakfast and taking antihypertensive medications, and after urination and defecation. Before blood pressure measurement, all patients will be required to rest for at least 5 min. Blood pressure is measured using the YUYUE electronic sphygmomanometer (YE660A, China). Researchers will collect blood pressure data once a month.Protocol-noncompliance: If the patient’s SBP does not reach the assigned target during follow-up, the cardiologists will evaluate the patient according to the predefined antihypertensive treatment algorithm (Figures 2, 3).Unable to complete the required CTA examinations: We will contact each patient one month before the CTA examination by telephone to ensure completion. If patients are unable to complete CTA examinations in the required time interval, they will not be included in the final analysis.

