### Safety monitoring

Each participating investigator has primary responsibility for the safety of the individual participants under his/her care. At each follow-up, CRC will specifically query participants for adverse events (AE) and serious adverse event (SAE) and recorded them in the case report form (CRF). Event Adjudication Committee members are responsible to make final ascertain of safety outcomes.

In our current study, adverse event (AE) is defined as any intervention related unfavorable medical outcomes, including any clinically obvious symptom, abnormal sign, or disease. In our current study, we will monitor AE including hypotension, dizziness, angioedema, headache.

Adverse event is considered as serious adverse event (SAE) only when it met following criteria: fatal or life-threatening, result in significant or persistent disability, or require hospitalization or surgical intervention, including:

Symptomatic hypotension.Arrhythmia.Acute kidney failure.Electrolyte abnormalities.Injurious falls.Syncope.Unexpected events for which the investigator believes that intervention caused the event or contributed to the immediate cause of the event.

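### The rupture definition has no route for a fatal rupture without CT, MRI or CSF proof, so such deaths drop out of the rupture outcome and usually out of the primary composite

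*Protocol article*

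**What the plan says.** Outcomes and relative definitions sets the primary endpoint: "The primary efficacy outcome is UIA instability, including aneurysm growth, rupture or aneurysm-related symptoms during 24-month follow-up". Its rupture component begins "Aneurysm rupture is diagnosed when patients have the symptoms of non-traumatic subarachnoid hemorrhage (e.g., severe headache and sudden coma) attributable to the target UIA" and continues, after a comma, with "imaging evidence of hemorrhage on CT or MRI, and/or bloody cerebrospinal fluid from lumbar puncture". The first secondary outcome is "UIA rupture events during 24-month follow-up". All-cause death and death attributed to the aneurysm appear in neither list. Two blinded investigators assess instability.

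Three other statements decide what happens to a patient who dies without a test:

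- Quality control of the research: "If patients are unable to complete CTA examinations in the required time interval, they will not be included in the final analysis". No exception is made for death.
- Endpoint and outcome evaluation: "Patients who do not meet the requirement of quality control may be further excluded based on the consensus of the investigators’ discussion". The same section plans Cox regression and does not mention death.
- Safety monitoring: "Event Adjudication Committee members are responsible to make final ascertain of safety outcomes". As written, the committee's task does not extend to efficacy events.

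**The concern.** The trial is meant to prevent rupture, and its gravest form is one that kills before the patient reaches a scanner. On the natural reading (symptoms plus confirmation), that patient does not meet the definition. If nobody saw the collapse, the symptom element is missing as well. The CTA rule then removes the patient or, if it is not applied, the Cox model would ordinarily censor follow-up at death. Either way the event is not counted.

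At stake are the completeness of the rupture secondary outcome, which has far fewer events than the composite, and the handling of sudden deaths in an open-label trial. If the rule is left open, those deaths will be classified after the data exist.

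**Working it through.** **Reading the definition.** The comma list ending in and/or can be read in two ways.

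- Symptoms plus at least one of imaging or CSF: a death before any test fails, whether witnessed or not.
- Any one element is enough: a witnessed collapse attributed to the aneurysm could count. An unwitnessed death still fails, and a severe headache attributed to the aneurysm could qualify as rupture with no proof of bleeding.

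Neither reading captures every fatal rupture, and two assessors could classify the same death differently.

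**Other efficacy components.** Growth needs imaging. Of the symptom components, sentinel headache is the likeliest to apply. It could bring a death preceded by a reported headache into the composite, but not into the rupture outcome.

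**Planned figures.** Inputs from Sample size: control risk 20.7%, 50% reduction (so 10.35%), α = 0.05, 0.90 (printed as β, but it works only as power), 10% dropout. The two-sided test comes from Endpoint and outcome evaluation. With unpooled variance:

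n = (1.960 + 1.282)² × (0.207×0.793 + 0.1035×0.8965) / 0.1035² = 10.507 × 0.25694 / 0.010712 = 252.03, rounded up to 253 per arm. Dropout: 253/0.9 = 281.1, rounded up to 282. Both match the plan.

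**Expected loss.** Events: 253×0.207 = 52.4 and 253×0.1035 = 26.2, total 78.6. The document gives neither the share of events that are ruptures nor the share of ruptures that die untested, so both are assumed:

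- Ruptures at 5-20% of events: 3.9 to 15.7.
- Of these, 10-20% without CT, MRI or CSF evidence: 3.9×0.10 = 0.4 to 15.7×0.20 = 3.1 events lost.

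The abstract's 60% reduction changes little: 52.4 + 20.9 = 73.3 events, hence 0.4 to 2.9 lost.

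**Power.** Let m be the assumed share of control patients with an uncounted fatal rupture over 24 months, with half that share in EBPL. With 253 per arm and the pooled two-proportion formula, power with full capture is 0.898.

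| m | uncounted, SBPL + EBPL | power if kept without an event | power if excluded |
|---|---|---|---|
| 0.1% | 0.25 + 0.13 | 0.896 | 0.896 |
| 0.5% | 1.27 + 0.63 | 0.889 | 0.891 |
| 1% | 2.53 + 1.27 | 0.880 | 0.885 |
| 2% | 5.06 + 2.53 | 0.860 | 0.870 |

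A loss of 0.4 to 3.1 events corresponds to m of about 0.1% to 0.8% (3.1 / (253×1.5) = 0.8%), so power stays at about 0.88 or above.

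**Direction.** Suppose 10 versus 5 true ruptures, with 20% lost in each arm. That leaves 8 versus 4: the ratio stays 0.50 while the difference falls from 5 to 4. For the composite, losing 2 and 1 gives 50.4 versus 25.2, still 0.50. With exclusion at m = 1%, the risks are (0.207−0.01)/0.99 = 0.1990 and (0.1035−0.005)/0.995 = 0.0990, a ratio of 0.497.

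**The case against.** The case against is substantial, and much of it stands.

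- **Scored as event-free.** A reader might infer that these patients count as free of the event. The document does not say so. Its only explicit rule leads to exclusion, and a Cox model would ordinarily censor at death. The event is lost, but not by being recorded as a non-event.
- **Imaging after death.** The text sets no ante-mortem limit on CT or MRI, so a post-mortem scan could meet the imaging element. The document does not reject such evidence; it leaves it unsettled.
- **Contrast with myocardial infarction.** That definition lists "angiography or autopsy evidence of intracoronary thrombus", which tempts one to allege an inconsistency. There, autopsy only supplements a required biomarker rise, so an untested death at home would fail that definition too. No contradiction follows.
- **Bias towards no effect.** More losses in SBPL is what equal proportional loss produces if EBPL works. It does not pull the hazard ratio towards 1, and the documents give no reason to expect different loss rates by arm.
- **Specificity.** A broad probable category would admit sudden deaths from other causes, and false positives in both arms dilute a hazard ratio. This is a good reason to keep that category out of the main analysis.
- **Condensed article.** Adjudication of deaths and competing-risk methods may sit in documents not shown, and their absence is no finding. What remains is that the printed definition and the printed exclusion rule, applied as they stand, lose these events.

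**Conclusion.** The point holds as a limited but real defect in the endpoint rule. A fatal rupture without CT, MRI or CSF evidence has no secure route into the rupture secondary outcome. It usually misses the composite too, unless a reported headache qualifies as sentinel headache or a looser reading of the and/or list is adopted.

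The expected loss is about 0.4 to 3 of 78.6 planned events. It rests wholly on the two assumed shares, and the loss of 10-20% of ruptures is itself one of those assumptions. The effect on the power of the composite is minor. The hazard ratio stays about the same if loss is proportional across arms and EBPL lowers rupture risk as it lowers the composite. Rupture incidence and the absolute difference are understated, precision falls, and every lost event is a fatal one.

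**What to change.** 1. Reword the definition: rupture requires attributable symptoms plus CT/MRI or CSF evidence of hemorrhage, OR subarachnoid hemorrhage from the target aneurysm at autopsy or on post-mortem imaging.
2. Exempt patients who die from the CTA-completion exclusion in Quality control of the research, and keep their follow-up to death.
3. Have the blinded assessors classify other unexplained sudden deaths as probable fatal rupture where the evidence supports it. Use that category only in a pre-specified sensitivity analysis (definite versus definite plus probable).

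The cost is a few sentences and one extra analysis, with no change to the planned 253 per arm (282 after dropout). A few sudden deaths from other causes may enter the probable category; separate reporting makes that visible. The wording should be fixed before any outcome data are seen.
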